### Study procedures and follow-up

Eligible patients are included within the first 24 h of admission. Baseline measurements are carried out within 48 h from admission. In-person follow-up visits are conducted three months (+/- 1 week) and 12 months (+/- 2 weeks) after inclusion. An MRI is performed in extension to the 12-month follow-up visit. If patients decline to participate in the MRI or if they have incurred contraindications to undergo MRI, they are still eligible for the 12-month follow-up visit. In addition, long-term register-based follow-up is planned. It will include follow-up for recurrent stroke, other vascular events, vascular death, and dementia. Study procedures and their timings are listed in Table 2. Figure 1 illustrates anticipated patient inclusion and follow-up.

**Table 2 Tab2:** Study assessments and registrations

Assessment/registration	Baseline	3-month follow-up	12-month follow-up	Long-term follow-up
Demographics	x			
Medical history	x			
Medication use	x			
Admission NIHSS score	x			
Symptom onset and admission time	x			
Acute treatment	x			
Standard blood chemistry at admission	x			
Pre-stroke mRS	x			
IQCODE	x			
Height, weight and BP	x	x	x	
Smoking and alcohol use	x			
MoCA	x	x	x	
PASE	x	x	x	
WHO-5	x	x	x	
MDI	x	x	x	
Educational level	x			
New vascular events		x	x	x
Functional outcome: mRS		x	x	
Stroke classification: TOAST and OSCP		x		
RBANS		x	x	
Blood sample for EVs*	x	x		
Blood sample for APOE genotyping		x		
MRI**	x		x	
Dementia				x

**Blood sample for EVs is drawn 24 h (+/- 8 h) after admission*

***Baseline MRI is performed 24 h (+/- 6 h) after acute MRI on admission*

*NIHSS: National Institutes of Health Stroke Scale, mRS: modified Rankin scale, IQCODE: Informant Questionnaire on Cognitive Decline in the Elderly, BP: blood pressure, MoCA: Montreal Cognitive Assessment, PASE: Physical Activity Scale for the Elderly, WHO-5: World Health Organisation Five Well-Being Index, MDI: Major Depression Inventory, TOAST: trial of Org 10,172 in Acute Stroke Treatment, OSCP: Oxfordshire Community Stroke Project Classification, RBANS: Repeatable Battery for the Assessment of Neuropsychological Status, EVs: extracellular vesicles, APOE: apolipoprotein E, MRI: magnetic resonance imaging*

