### Cognitive assessments

Post-stroke cognitive function is assessed at three and 12-month follow-up visits using the Repeatable Battery for the Assessment of Neuropsychological Status (RBANS). To reduce learning bias, version A is administered at the three-month visit and version B is administered at the 12-month visit. All assessments are done by trained personnel. Training and scoring are overseen by a neuropsychologist and a neurologist specialized in dementia. All RBANS measures are administered and scored using standard procedures detailed in the Danish manual. The RBANS is a validated repeatable assessment of cognitive function [39, 40]. With 12 subtests it covers the five cognitive domains: immediate memory, visuospatial function, language, attention, and delayed memory. Based on norm data, the RBANS provides sub scores and age-adjusted index scores for each domain and combine them to a total index score.

The Montreal Cognitive Assessment (MoCA) is administered at baseline and at three- and 12-month follow-up. The MoCA is a brief cognitive screening tool validated for post-stroke cognitive impairment [41].

Pre-stroke cognition is assessed by the short version of the Informant Questionnaire on Cognitive Decline in the Elderly (IQCODE). The IQCODE is a validated 16-item questionnaire assessing change in cognition over the course of 10 years [42]. It assesses changes in working, short-term and long-term memory, learning and attention and the ability to perform daily activities. The questionnaire is completed by the nearest relative either in person or by telephone interview. The respondent is asked to rate the change in the patient’s cognitive ability before the AIS or TIA.

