### Statistical analysis

The role of capillary dysfunction on PSCI will be assessed by the association between CTH at baseline and PSCI. The primary outcome will be the difference in total RBANS score from three to 12 months follow-up. Secondary outcomes include total RBANS score at 12 months follow-up, difference in MoCA score from three to 12 months follow-up, and MoCA score at 12 months follow-up. All associations will be assessed using linear mixed effects models adjusting for age, sex, educational level, baseline NIHSS, smoking, and diabetes. Analyses will be stratified by APOE genotype (ε4 carriers vs. non-carriers) and pre-stroke cognitive decline (IQCODE > 3.48 vs. IQCODE ≤ 3.48) to assess for effect modification by these factors. Level of cSVD will be assessed as a mediator.

Associations between EV characteristics and cognitive function after stroke will be assessed primarily by exploring differences in EV characteristics at baseline between patients with normal cognition, impaired cognitive function (total RBANS index score 70–85) and reduced cognitive function (total RBANS index score < 70) at 12-month follow-up using analysis of differential expression. Secondary analyses include exploring differences in EV characteristics at baseline among patients with a decline (≥ 6 points) versus patients with no decline in total RBANS score from three to 12 months, between patients with decline (≥ 2 points) versus no decline in MoCA score from three to 12 months follow-up, and between patients above and below MoCA score of 22 and 26 at 12-months follow-up. Analyses will be adjusted for age, sex, educational level, baseline NIHSS, diabetes, and hypertension. In addition, analyses stratified by APOE genotype, pre-stroke cognitive decline, and level of cSVD will be performed.

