## Discussion

With the ENIGMA study we aim to study vascular contributions to cognitive decline and dementia. Using advanced MRI techniques and studying EV characteristics, we aim to investigate capillary dysfunction and EV characteristics as predictors of cognitive decline and cognitive function one year after AIS and TIA.

It is well established that ischemic stroke and cSVD increase risk of cognitive impairment and dementia [5, 51]. However, mechanisms behind vascular cognitive impairment are largely unknown. For this reason, numerous prospective observational studies are examining predictors of post-stroke cognitive decline [52–58] and consortia have been established to drive the research into vascular cognitive impairment forward [59, 60]. With ENIGMA we hope to provide novel knowledge about the microvascular mechanisms behind PSCI and the potential of EVs as biomarkers of the vascular brain reserve and consequently post-stroke cognitive function.

Traditionally, we consider stroke and TIA flow-limiting conditions. However, increasing evidence suggests that we should also consider dysfunction of the capillaries, primarily limiting oxygen extraction rather than blood supply, as an important mechanism of cerebrovascular disease [20, 61]. Capillary dysfunction has been shown to contribute to tissue injury after acute stroke and to cognitive impairment in both vascular dementia and Alzheimer’s disease [21, 48, 61, 62]. New imaging methods, developed by researchers in our group, now enable us to characterize microvascular flow patterns on MRI with the potential to detect and quantify the preclinical manifestations of this contribution to cerebrovascular disease [22, 24]. In addition, advanced diffusion-weighted MRI methods such as diffusion kurtosis imaging may contribute to a better understanding of the microstructure and functional integrity of brain tissue.

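### Baseline MoCA is in neither covariate list, so the 12-month level analyses cannot show whether CTH or an EV marker predicts one-year cognition beyond the deficit already measured at baseline

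*Protocol article*

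**What the plan says.** **Collection.** Under Cognitive assessments: "The Montreal Cognitive Assessment (MoCA) is administered at baseline and at three- and 12-month follow-up". Table 2 agrees. On timing, Study procedures and follow-up states: "Baseline measurements are carried out within 48 h from admission". The baseline MRI (24 h after the admission scan) and the first EV sample (24 h after admission) belong to the same early period. RBANS is first given at three months.

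**Outcomes (Statistical analysis).** For CTH: "The primary outcome will be the difference in total RBANS score from three to 12 months follow-up". The secondary outcomes are the 12-month RBANS, the MoCA change from three to 12 months, and the 12-month MoCA. For EVs, the main comparison is between three groups defined by 12-month RBANS. Secondary comparisons include a split "between patients above and below MoCA score of 22 and 26 at 12-months follow-up".

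**Covariates.** For CTH: "All associations will be assessed using linear mixed effects models adjusting for age, sex, educational level, baseline NIHSS, smoking, and diabetes". For EVs: "Analyses will be adjusted for age, sex, educational level, baseline NIHSS, diabetes, and hypertension". IQCODE appears only as a stratifier.

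**Aim.** The Discussion says "we aim to investigate capillary dysfunction and EV characteristics as predictors of cognitive decline and cognitive function one year after AIS and TIA". The Abstract's background also speaks of finding markers that can predict PSCI.

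**The concern.** The study holds an early score on the same instrument as one of its 12-month outcomes and gives it no analytic use, because every MoCA change is counted from three months. No listed covariate replaces it. NIHSS measures neurological severity, and IQCODE is an informant's rating of change before the event. Both covariate lists are explicit, so this is a stated choice and not a detail left to an analysis plan.

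What is at stake is the meaning of the word predictor. If CTH or an EV marker is associated with 12-month cognition only because it tracks a deficit visible at the bedside in the first two days, the listed models will still report an association. A reader looking for a prognostic aid could take that as information beyond a short cognitive test.

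**Working it through.** **Inputs from the article.** 100 patients with complete follow-up, significance level 0.05, CTH plus six covariates. The article gives no correlation involving MoCA, so every correlation below is an assumption.

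**The plan's own figure.** The sample size of 71 (10 predictors, 90% power) corresponds to an overall F test with f² = 0.335, that is R² = 0.25. An assumed correlation of 0.50 (f² = 0.333) gives 72. The effect size is not stated, so 71 is plausible but cannot be verified. This point does not depend on it.

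**1. A marker that adds nothing beyond baseline MoCA.** Let the marker correlate a = 0.3 with baseline MoCA, and baseline MoCA correlate ρ = 0.6 with 12-month MoCA, with no other link and no other covariates.

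- Marginal correlation of marker and outcome: 0.3 × 0.6 = 0.18.
- CTH, N = 100, Fisher z: atanh(0.18) × √97 = 0.182 × 9.849 = 1.79. P(Z > 1.96 − 1.79) ≈ 43%. A simulation of 3,000 samples gives 44%.
- EV, two groups with 40% in the low group (assumed): dichotomising multiplies the correlation by 0.386/√(0.4 × 0.6) = 0.789, giving 0.142. Then atanh(0.142) × 9.849 ≈ 1.41 and P(Z > 0.55) ≈ 29%. The simulation gives 31%.
- With baseline MoCA in the model, both fall to about 5%.
- Range for CTH: 17% (a = 0.2, ρ = 0.5) to 81% (a = 0.4, ρ = 0.7).

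**2. Precision, CTH models of 12-month level.** The residual variance is multiplied by 1 − ρ². At ρ = 0.5 that is 0.75, or 25% lower. The SE is multiplied by √0.75 = 0.87, and 100 patients act like 100/0.75 = 133. For an assumed partial correlation of 0.25 between CTH and outcome, power rises from 72% (7 predictors) to 85% (8 predictors), provided that CTH is unrelated to baseline MoCA.

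If CTH instead correlates 0.2 with baseline MoCA in the same direction, the partial correlation becomes (0.25 − 0.2 × 0.5)/√((1 − 0.04)(1 − 0.25)) = 0.15/0.849 = 0.177. Power is then 43%, because the adjusted coefficient is a smaller quantity. The SE gain also shrinks as this correlation grows. At ρ = 0.6 the simulated SE goes from 0.100 to 0.085 for a = 0.3, but only from 0.096 to 0.094 for a = 0.5.

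**3. Precision, EV models.** Here the EV level is the dependent variable, and baseline MoCA is collinear with the outcome group. With ρ = 0.6 the group–baseline correlation is 0.6 × 0.789 = 0.473, so the SE is inflated by 1/√(1 − 0.473²) = 1.135. The simulated SE rises from 0.203 to 0.232 for an unrelated marker, and from 0.201 to 0.222 for a = 0.3.

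**4. Change from three to 12 months (MoCA).** If the three- and 12-month scores correlate 0.75, the correlation of baseline with change is (r₁₂ − r₃)/√(2 − 1.5). For r₃ = r₁₂ = 0.6 it is 0. For r₃ = 0.7 and r₁₂ = 0.5 it is −0.28. The SE multiplier is 1.00 to 0.96, so there is little or nothing to gain. For the primary RBANS change the article gives no basis for expecting any gain.

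**The case against.** The strongest objection concerns the estimand. The objectives are worded as associations, and the analysis of CTH is mechanistic, with cSVD treated as a mediator. Baseline MoCA is taken after the stroke, while capillary dysfunction is described as related to age and risk factors and so plausibly precedes it. The score may lie on the pathway, and conditioning on it would remove early effects of the marker. This stands: leaving baseline MoCA out of the main model is defensible, and replacing the listed model would be contestable. It does not dispose of the point, because the article also calls the markers predictors and no listed analysis can support a claim of added prediction.

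Three stronger readings are tempting and are not supported:

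- *The study as a whole loses precision.* Not so. The EV standard errors would rise, the change models would barely move, and power in the CTH level models can fall if CTH tracks baseline MoCA.
- *The 43% is a false-positive rate.* It is the power to detect a real marginal correlation of 0.18. The 5% answers a different question.
- *The primary CTH result is compromised.* That outcome is the RBANS change from three to 12 months, which this point leaves alone.

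Two further cautions are fair. The calculations omit age, education and NIHSS, which probably share variance with baseline MoCA, so the planned models' own figures would differ. A mixed model could also carry baseline MoCA as a repeated outcome, but the text does not say so.

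**Conclusion.** The point holds as a gap between aim and analysis for the 12-month level outcomes. These are the two secondary level outcomes for CTH, and the EV contrasts by 12-month RBANS group (the main EV comparison) and by 12-month MoCA. As planned, these analyses show total association only and cannot support a claim that a marker adds to an early bedside score. The 43%, 28–31% and 5% show how far the two questions can diverge; they rest on assumed correlations and say nothing about error rates in the planned tests. The precision argument is secondary and limited to the CTH level models with at most a weak CTH–MoCA correlation. For EVs the case is incremental prediction alone. This is a worthwhile addition, not an error that invalidates the listed models.

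**What to change.** Keep the listed models and label them as the total association. Beside them, pre-specify a second model that adds baseline MoCA as a continuous covariate for:

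- CTH with 12-month MoCA and 12-month total RBANS;
- the EV contrasts by 12-month RBANS groups and by the 12-month MoCA cut-points.

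Rest only claims of added (incremental) prediction on the second model, and state that it excludes effects already present at baseline. Leave the three-to-12-month change models as they are.

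**Cost.** No new data, one degree of freedom, and one further reported model per level outcome. CTH plus six covariates counts as seven predictors if each is one term, so an eighth fits within the 10 allowed for in the sample size calculation. Some patients will lack a baseline MoCA, for example because of aphasia. This should be handled by multiple imputation and not by a missing indicator, which can bias estimates in observational data. Expect modestly wider standard errors in the EV models.

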## Introduction and rationale

We continue to live longer, and the impact of age-related diseases such as stroke and dementia is growing [1]. In addition to the functional disability a stroke may cause, cognitive impairment after stroke is common. Post-stroke cognitive impairment (PSCI) is observed in up to 50% of stroke survivors, and a stroke doubles the risk of dementia [2–4]. Persistent cognitive impairment has also been found in patients with transient ischemic attack (TIA) [5], a disorder that is considered reversible by definition.

PSCI and dementia are associated with increased morbidity and mortality [6–8], however no specific disease modifying management exist. This has urged stakeholders to call for more research into the epidemiology, risk-factors, biomarkers, and mechanisms underlying PSCI [9, 10].

Many risk factors for PSCI have been identified including stroke severity, lesion size and location and common vascular risk factors such as age, hypertension, diabetes, atrial fibrillation, and smoking [5, 11–13]. Further, some magnetic resonance imaging (MRI) markers have been associated with PSCI including brain atrophy and markers of cerebral small vessel disease (cSVD) such as white matter hyperintensities and cerebral microbleeds [14, 15]. In addition, several blood-derived biomarkers have also shown promise as predictors of PSCI [16–18]. Despite these advances in the field, the exact underlying pathophysiology behind PSCI is not well understood. Identification of early pathologic changes associated with PSCI could be a first step in the development of a prognostic aid and in identifying future therapeutic targets.

Cerebral capillary dysfunction is characterized by limited oxygen extraction from the brain capillaries due to age- and risk factor-related capillary flow heterogeneity [19]. Capillary dysfunction is a pathophysiological feature of cSVD and may play an important role in the vascular mechanisms underlying PSCI [20, 21]. Advanced perfusion magnetic resonance imaging (MRI) techniques can detect and quantify capillary dysfunction and may help identify markers of PSCI [22–24].

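### The CTH models leave out hypertension, although the protocol names it as a PSCI risk factor and adjusts for it in the EV analyses

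*Protocol article*

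**What the plan says.** The Statistical analysis section of the protocol article states that the role of capillary dysfunction "will be assessed by the association between CTH at baseline and PSCI". On the outcome it says: "The primary outcome will be the difference in total RBANS score from three to 12 months follow-up". The CTH models, primary and secondary, are linear mixed effects models "adjusting for age, sex, educational level, baseline NIHSS, smoking, and diabetes". "Level of cSVD will be assessed as a mediator"; no other mediator is named.

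For the EV analyses the same section gives another set: "Analyses will be adjusted for age, sex, educational level, baseline NIHSS, diabetes, and hypertension". Five covariates are common to both sets. The CTH set adds smoking and the EV set adds hypertension. No reason is given for the difference.

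The Introduction and rationale lists known risk factors for PSCI: "stroke severity, lesion size and location and common vascular risk factors such as age, hypertension, diabetes, atrial fibrillation, and smoking". It attributes the limited oxygen extraction in capillary dysfunction to "age- and risk factor-related capillary flow heterogeneity".

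**The concern.** A covariate related to both exposure and outcome can produce, inflate or mask an association if it is left out. The protocol links vascular risk factors to capillary flow heterogeneity (the exposure) and to PSCI (the construct behind the outcome). Smoking and diabetes stand in the same list as hypertension and are adjusted for. Hypertension is dropped only in the analysis where capillary dysfunction is the exposure.

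The study wants to attribute a CTH–RBANS association to capillary dysfunction. If patients with hypertension have both higher CTH and a different course of RBANS, part of the association could reflect hypertension. A larger sample would not remove such a bias.

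**Working it through.** **1. The covariates side by side**

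| Covariate | Named as PSCI risk factor (Introduction) | CTH set | EV set |
|---|---|---|---|
| Age | yes | yes | yes |
| Stroke severity / NIHSS | yes | yes | yes |
| Diabetes | yes | yes | yes |
| Smoking | yes | yes | no |
| Hypertension | yes | **no** | yes |
| Lesion size | yes | no | no |

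Sex and educational level are in both sets. For hypertension the CTH set departs from both the Introduction and the EV set. For lesion size the two sets agree.

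**2. Are the data there?** Medical history, medication use and blood pressure are baseline items (Table 2; Additional assessments). The EV analyses need a hypertension variable in any case.

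**3. Is there room in the model?** The Sample size calculation gives 71 patients for 10 predictors, 90% power and significance level 0.05, without a numerical effect size. The figure therefore cannot be reproduced independently, but the effect size can be solved back from it. With u predictors, v = N − u − 1 and noncentrality f² × (u + v + 1) = f² × N, setting u = 10, N = 71 and power 0.90 gives f² = 0.335, so R² = 0.335 / 1.335 = 0.251 and r = 0.50. Starting from an assumed r = 0.50 gives N = 72, so 71 is plausible.

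CTH plus six covariates is 7 terms if each takes one degree of freedom; with hypertension it is 8. Holding f² = 0.335:

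| Predictors | N for 90% power | Power at N = 100 |
|---|---|---|
| 7 (as listed) | 63 | 99.3% |
| 8 (with hypertension) | 66 | 99.1% |
| 10 (as budgeted) | 71 | 98.4% |

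If the calculation is read instead as a one-degree-of-freedom test of the CTH coefficient, the back-solved f² is 0.175 and the required N is 68, 69 and 71. On either reading the added covariate fits well within the planned 100 patients.

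**4. How large could the bias be?** The documents supply no inputs, so this is illustration only. For a binary omitted covariate with prevalence p, a CTH difference of d1 SD and an outcome difference of d2 SD, the standardised CTH coefficient shifts by p(1 − p) × d1 × d2. Both differences must be net of the covariates already in the model, and d2 must refer to the outcome analysed.

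- Assumed p = 0.60: p(1 − p) = 0.24.
- Low end, d1 = 0.3 and d2 = 0.2: 0.24 × 0.06 = 0.014.
- High end, d1 = 0.6 and d2 = 0.4: 0.24 × 0.24 = 0.058.

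More generally, an omitted standardised covariate correlated a with CTH and with partial effect b on the outcome shifts the coefficient by a × b. For a and b each between 0.1 and 0.3 that is 0.01 to 0.09.

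For comparison, the smallest partial correlation detectable with 90% power at N = 100 is about 0.31, whether the model has 7 or 8 predictors. The high-end hypertension figure is 0.058 / 0.31 = 0.19 of that.

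**The case against.** **The two analyses differ.** The primary CTH outcome is the change in total RBANS from three to 12 months. The primary EV analysis compares EV characteristics across three categories of RBANS at 12 months. Confounders depend on the exposure and outcome in question, so two different sets are not in themselves a contradiction. This stands, and the point does not rest on the sets being identical. It rests on the protocol's own account of hypertension. The difference in outcome also explains little: RBANS at 12 months is a secondary CTH outcome, and RBANS decline from three to 12 months is a secondary EV comparison.

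**The outcome is a change.** A constant effect of hypertension on RBANS level cancels in a difference between two visits; only an effect on the course confounds the primary analysis. The Introduction speaks of risk factors for PSCI, not for that change. This stands and limits what can be claimed for the primary outcome. It does not apply to the secondary outcomes at 12 months, which use the same covariates.

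**A condensed article.** Reasons for covariate choice may be given elsewhere. But the article states the set itself, and the set is what is questioned.

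**Two stronger readings.** A reader might infer that the primary association is confounded as planned. The documents show only a risk, of unknown size. A reader might also infer that infarct volume belongs in the primary model, since lesion size is a listed PSCI risk factor and CTH is measured on an MRI about 24 h after the admission scan. The protocol does not support that. Its Discussion puts the arrow the other way: "Capillary dysfunction has been shown to contribute to tissue injury after acute stroke". Lesion volume may thus lie on the causal path, and routine adjustment could remove part of the effect under study. An influence of the infarct on measured CTH is possible but nowhere stated. NIHSS partly covers lesion size, the EV set omits it too, and no lesion-volume measurement is described.

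**Conclusion.** The point holds for hypertension. By the protocol's own account it is a risk factor for PSCI and belongs to the class of factors related to capillary dysfunction. It can be derived from data already collected and is adjusted for in the EV analyses, yet it is missing from the CTH models without a reason. The consequence is an avoidable risk of residual confounding.

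Its size cannot be computed from the documents. The illustrative 0.014 to 0.058 rests on an assumed prevalence and assumed differences in CTH and in the RBANS outcome. If hypertension affects RBANS level but not its change, or if the included covariates already carry most of its effect, the shift in the primary analysis would be smaller. The probable size is modest. The case for change is that the remedy costs almost nothing, not that the result is known to be biased.

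**What to change.** - Add baseline hypertension to the covariate set of the CTH models, with the same stated definition as in the EV analyses. Enter it in the same form as the other six covariates, so that it bears on the change from three to 12 months and not only on the level.
- Report the six-covariate model as a sensitivity analysis.
- If hypertension is deliberately left out, state the causal reasoning.
- Keep DWI lesion volume out of the primary model. At most, show CTH results with and without it as a sensitivity analysis, and say that it may be a mediator.

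The cost is one sentence in the analysis plan and one degree of freedom: CTH plus seven covariates makes 8 terms against 10 budgeted, if each takes one degree of freedom. No new data are needed for hypertension. The optional lesion-volume analysis would need lesion outlining on the DWI already acquired, if that is not done anyway.

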### Sample size calculation

A previous study could show a correlation between capillary dysfunction and cognitive status in 32 patients with Alzheimer’s disease [48]. To find a similar effect size in a linear model with 10 predictor variables, a sample size of 71 patients is needed (90% power, significance level 0.05). This calculation was performed using the pwr-package in *R* version 4.3.2 [49]. Previous studies of EV characteristics were able to distinguish between stroke severity, lesion volume and outcome when comparing groups of 21 and 20 stroke patients [50]. A sample size of 100 patients with complete follow-up is therefore considered adequate.

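### Effect modification by APOE ε4 and IQCODE is to be assessed by stratified CTH analyses alone, which give no test or interval for the difference between strata

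*Protocol article*

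**What the plan says.** All references are to the protocol article.

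- **Outcome** (Statistical analysis): "The primary outcome will be the difference in total RBANS score from three to 12 months follow-up".
- **Model** (same section): "All associations will be assessed using linear mixed effects models adjusting for age, sex, educational level, baseline NIHSS, smoking, and diabetes". Neither APOE nor IQCODE is in this adjustment list, and no product term is named.
- **Effect modification** (same section): "Analyses will be stratified by APOE genotype", carriers against non-carriers, and by IQCODE above 3.48 against 3.48 or below, "to assess for effect modification by these factors".
- **Size** (Sample size calculation): for an overall association, "a sample size of 71 patients is needed (90% power, significance level 0.05"), and 100 patients with complete follow-up are planned. Nothing is given for strata or for an interaction.

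**The concern.** The text fixes both a goal, effect modification, and a method, stratification. The goal concerns whether the CTH slope differs between two groups of patients. Stratification returns one slope per group, each with its own p-value, and leaves the difference between them without an estimate, interval or error rate.

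Two strata cut from about 100 patients can easily disagree on significance because one is smaller, or by chance, even when the slopes are the same. The risk is a published statement that APOE or pre-stroke cognitive decline modifies the role of capillary dysfunction when the data show only unequal precision.

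**Working it through.** **The plan's own figure.** The article gives N = 71 but no numerical effect size, so the figure can only be solved backwards. Using the noncentral-F power of a linear model with u = 10 predictors, v = 71 − 10 − 1 = 60 and λ = f²(u + v + 1), 90% power at 0.05 needs f² = 0.335. That is R² = 0.335/1.335 = 0.25, or r of about 0.50. For comparison, f² = 0.30 gives N = 79 and f² = 0.35 gives N = 69. So 71 is internally consistent and concerns the overall association only.

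**Inputs for the check**
- From the article: N = 100, CTH plus six covariates, α = 0.05 (taken as two-sided).
- Assumed: the share of patients in the smaller stratum (15% to 50%) and the partial correlation r of CTH with the outcome (0 to 0.5), the same in both strata. The article gives neither.
- An ordinary linear model, which matches one change score per patient.

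**Formulas.** Effect size f² = r²/(1 − r²), so r = 0.3, 0.4 and 0.5 give 0.099, 0.190 and 0.333. If a and b are the probabilities of significance in the smaller and larger stratum, the strata disagree with probability a(1 − b) + b(1 − a).

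Worked example, r = 0.3 and a 25% stratum: a = 0.247 and b = 0.727, so 0.247 × 0.273 + 0.727 × 0.753 = 0.067 + 0.547 = 0.61.

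**Simulation** (4,000 runs per cell). Share of studies in which exactly one stratum is significant, with no true effect modification:

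| Smaller stratum | r = 0 | r = 0.3 | r = 0.4 | r = 0.5 |
|---|---|---|---|---|
| 15% | 10% | 70% | 79% | 71% |
| 20% | 10% | 66% | 67% | 53% |
| 25% | 10% | 61% | 58% | 39% |
| 30% | 9% | 56% | 49% | 28% |
| 50% | 10% | 49% | 33% | 11% |

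On the same data, a test of the CTH-by-stratum product in the full-sample model rejected in 4.8% to 5.6% of runs in every cell.

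**Power of the interaction test.** With a share p in one stratum, the standard error of the interaction is 1/√(p(1 − p)) times that of the main effect: 2.5 at p = 0.20 and 2.0 at p = 0.50. For an interaction as large as a main effect that has 90% power, power is Φ((1.960 + 1.282)/ratio − 1.960):
- p = 0.20: Φ(1.297 − 1.960) = Φ(−0.663) = 25%
- p = 0.50: Φ(1.621 − 1.960) = Φ(−0.339) = 37%

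**The case against.** **The decision rule is not in the article.** Nothing there says the strata will be compared by significance in one and not the other, and the 50–80% depends on that reading. This stands. The figure measures what that reading would cost; it is not the error rate of a stated procedure.

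**Stratification does not itself create false effect modification.** The strata do not overlap, so their slopes are independent and can be compared from the two estimates and standard errors. A Welch-type comparison of the separately fitted slopes rejected in 4.5% to 5.5% of the same simulated runs. This also stands, so a reader should not infer that stratified fitting is invalid. What is missing is the comparison. Because the article offers stratification as the way to assess effect modification, this is more than detail left to an analysis plan.

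**The splits are unknown.** A reader might take it that both factors divide the cohort very unequally. Excluding known dementia makes a small group above 3.48 on IQCODE plausible, but it says nothing about APOE, and no split is given for either. The low corners of the table must be read with the high ones.

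**The extracellular vesicle (EV) analyses.** A reader might extend the point to them, since the article says "analyses stratified by APOE genotype, pre-stroke cognitive decline, and level of cSVD will be performed". That sentence does not give effect modification as its purpose, nor does it say which EV comparisons are stratified. The article also gives no expected share of patients below an RBANS score of 70 from which to count sparse cells. The point is therefore confined to CTH, and whether RBANS should be kept continuous in the EV analyses is a separate question.

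**Conclusion.** The concern holds for the CTH analyses. The article assigns the assessment of effect modification to stratified analyses and names nothing that would test or estimate the difference between strata.

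The size is conditional. For r of 0.3–0.4 and a smaller stratum of 15–30%, a one-significant-one-not reading would wrongly suggest effect modification in about 50–80% of studies for each modifier. It would do so in about 10% if CTH has no effect, or if r is about 0.5 with equal strata. Stratum shares, effect sizes and the reading itself are all assumptions.

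The primary overall CTH association and the planned sample size are not affected.

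**What to change.** For the CTH analyses, state that effect modification will be assessed in the full-sample model by adding the modifier's main effect and its product with CTH, in separate models for APOE ε4 and for IQCODE. Report each interaction estimate with its 95% CI. Show the stratum-specific CTH effects as descriptive only.

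Label these analyses exploratory: at N = 100 an interaction as large as a well-powered main effect would be detected only about 25–37% of the time, so a non-significant interaction should not be reported as absence of effect modification.

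The cost is two extra terms per model, because neither modifier is in the current adjustment list, and a change of wording. No further patients or data are needed.
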